**3. Scientific background**

As a consequence of demographic change the number of elders in road traffic also increases. A variety of age related illnesses like dementia, cardiovascular or musculoskeletal diseases lead to impairments in motoric, sensorial and cognitive functions1-3,8, some of which, like attention and executive function, are closely related to driving safety9,10. Traffic participants have to process visual, acoustic and tactile information simultaneously, react adequately to them, be stressable, estimate distances as well as correctly interpret traffic signs and judge their own driving abilities properly8. Studies could show that with increasing loss of cognitive functionality the risk of driving errors and accident frequency in road traffic rises4,5, the driving safety as a consequence decreases12,13. Especially in dementia, for example Alzheimer’s disease – the most common form of dementia14, which inevitably sooner or later leads to a loss of driving ability15,16 – and furthermore has a progressive process, the risk is particularly high17. Also the insight into illness is degraded18,19, which is why the self-reliant examination of one’s own driving ability in the context of duty to precaution and self review required by law in Germany is not guaranteed20. Already in early stages of dementia impairment should be taken into account. Studies point out that even mild cognitive impairment (MCI) can be accompanied by a decrease of driving competence. MCI describes the prodromal symptoms of dementia diseases, which comprises cognitive impairments, however does not lead to notable constraints in functioning independently. A general driving ban or broad restrictions for seniors with MCI nevertheless is inappropriate, especially considering that impairments in driving relevant cognitive domains may not be distinct enough to justify the revocation of the driver licence. The guidelines for assessment of driving fitness do not generally exclude the possibility of participation on road traffic; yet 13,6% of MCI-patients don’t pass an on-road driving test22.

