Generally, single tests are not appropriate as indicators for driving performance, as they do not provide a comprehensive picture of the driving behaviour, have no or only a low predictive value and cannot achieve high sensitivity or specificity values30,31. Single tests merely provide indications of possible limitations of driving ability, but they cannot replace an on-road driving assessment32-34. Bennett & Hons (2016)35 stated that there is not an exclusive cognitive domain that reliably and validly represents fitness to drive17. It led to the conclusion that a comprehensive test battery consisting of test-combinations and multiple instruments, which survey different driving relevant cognitive functions, constitutes the best predictor for driving ability in elders with mild cognitive impairment30,36,37. Nonetheless the insufficient clarification of the validity criteria of these test-batteries has to be mentioned38, which should be accomplished by further instruments proximal and distal to the construct.
Furthermore there is a large gap between scientific evidence and clinical application, mainly impeded by the missing cut-off values of the majority of research results29. Only few studies eventually generated scores which allowed for a distinction between “fit to drive” and “unfit to drive”. Latest recommendations imply a classification accuracy of 80-90%39 to guarantee a consistently accurate prediction. In addition, in contrast to the previous dichotomization between safe and unsafe drivers, a trichotomization is suggested29 which should categorize drivers into “safe”, “uncertain” and “unsafe”, with the middle category entailing a more detailed assessment for accurate classification, e.g. with the aid of an on-road driving assessment. Developing this screening-tool highest importance should be ascribed to an efficient implementation in clinical practice. In other words, it should not be resource-intensive in terms of time and personnel, therefore suggesting a computer or tablet-based application.

The following research hypotheses can be deduced:

(1) We assume that mild cognitively impaired and healthy subjects will differ significantly regarding on-road driving performance.
(2) Among assessed cognitive domains we expect especially visuospatial performance, attention and executive functions to predict driving ability.

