(3) We expect the newly developed screening-tool to differentiate with high diagnostic accuracy between safe and unsafe drivers. The accuracy is estimated at a minimum of 80% and should exceed the accuracy of single neuropsychological tests.
(4) Besides it is expected that driving competence will additionally be predicted by factors like age, driving experience in years and mileage per year.

**4. Study aims**The aim of the study is to develop a screening-tool with high predictive validity regarding driving ability of cognitively impaired subjects. Construct validity and criterion-based validity should be tested through a standardized on-road assessment as well as cognitive neuropsychological tests proximal and distal to the construct. The high practical relevance results from the necessity of a screening-tool for driving ability which is economically, validly and reliably applicable, tablet-based and thus mobile usable in medical care practice to support a low-threshold, qualitatively valuable and safe assessment of fitness to drive and counselling with respect to mobility; not least to meet legal requirements on the practitioner’s and patient’s side in this field.

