**6. Study design**
The study is designed as a monocentric, non-randomized cross-sectional-study at the kbo-Inn-Salzach-Klinikum Wasserburg/Inn. Cut-off-scores in the MMSE of < 27 and ≥ 18 allocate the participants to the experimental group of subjects with mild cognitive impairment. Subjects with a MMSE-score ≥ 27 will be assigned to the healthy control group. We expect the recruitment period to last about 24 months. Each of these groups undergo the same assessment procedure. Blinding is only possible for the driving instructor.

**7. Study population**Women and men with an age ≥ 50 years, who possess a valid driver licence and who are active drivers, i.e. have been driving regularly the last three month before participation, and speak fluently German language can participate in the study. Regarding possible use of medication an exact documentation and clarification of potential adverse effects on on-road driving should be carried out in the context of anamnesis. Subjects who are under dose escalation or medication shifts will be excluded. The consent ability has to be checked, doubts about it also lead to exclusion. 40 subjects with mild to moderate cognitive impairment and 40 healthy control subjects will be assessed, parallelized regarding age, education, sex, driving experience and mileage per year.

*General exclusion criteria for all participants (based on annex 4, statutory order of driving licences)*

- Current severe dementia (MMSE < 18)
- Current severe psychiatric, neurological or internistic disease
- Visual impairment (visual acuity worse than 60%; visual field <140°, double-vision, hemi-neglect)
- No fluent German in speech and writing

*Specific criteria for the experimental groups*Healthy subjects (CG):

- ≥ 50 years
- German as first language respectively German-speaking since early childhood
- MMSE ≥27
- No record of severe psychiatric or neurological diseases
- Currently no internistic disease
- Currently no radio- or chemotherapy for cancer treatment

Cognitively impaired subjects (EG):

- ≥ 50 years
- First language German respectively German-speaking since early childhood
- MMSE ≥18 and <27
- Patients from the following ICD-10 diagnosis groups
  - Organic, including symptomatic disorders (F00-F09), N=20
  - Affective disorders (F30-F39), N=10
  - Schizophrenia, schizotypal or delusional disorders (F20-F29) / Neurotic, stress-related and somatoform disorders (F40-F48), N=10

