**10. Biometry**

Examining the correlation between driving behavior and cognitive assessment in patients with neurological disorders studies indicate an average to large effect sizes for the TMT (part A and B) and visuospatial tests such as the Judgement of Line Orientation Test16,17,22,45. Therefore it can be assumed that TMT-L (part A and B) and LAT can predict driving behavior with an average effect size. The calculated sample size of N = 80 results as follows: Supposing a power (1 – β) of 80% and an alpha-level of α = .05 a sample size of N = 77 is necessary to detect an average effect calculating a multiple regression with three predictors (TMT-L part A, part B and LAT). In case of early dropouts we calculate a sample size of N=80 for recruitment.
Data will be analysed by means of multivariate analyses of variances followed by post-hoc-t-tests as well as regression analyses evaluating the predictive validity of the individual tests.
Premises of statistical calculations – such as normal distribution of sample or homogeneity of variance – shall be checked upfront.

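### Hypothesis 3 sets 80% overall accuracy as the tool's only numeric benchmark; at the protocol's only on-road failure rate, calling every driver safe exceeds it

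*Protocol*

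**What the plan says.** Hypothesis (3), at the end of Protocol section 3, expects the tool to "differentiate with high diagnostic accuracy between safe and unsafe drivers". It quantifies this once: "The accuracy is estimated at a minimum of 80" per cent. It adds that the tool's accuracy "should exceed the accuracy of single neuropsychological tests". The figure matches a recommendation cited earlier in the section: "Latest recommendations imply a classification accuracy of 80-90" per cent. Accuracy therefore reads as the overall proportion classified correctly.

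The same section gives the only on-road failure rate in the document: "13,6% of MCI-patients" do not pass. Section 7 sets the sample: "40 subjects with mild to moderate cognitive impairment and 40 healthy control subjects will be assessed". The impaired group covers MMSE 18 to 26 and several ICD-10 diagnosis groups.

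Section 8 g) describes the on-road assessment (WAFAB), which yields an 11-point rating with verbal categories and several error counts. The protocol does not say which WAFAB result makes a driver unsafe. Section 10 sizes the study for a regression and does not mention the accuracy benchmark.

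**The concern.** Overall accuracy depends on how common the unsafe drivers are. When they are few, a rule that ignores all test results and calls everyone safe is usually right. A fixed threshold below the accuracy of that rule (the no-information rate) says nothing about whether a tool can detect unsafe drivers.

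Section 4 makes development of this tool the aim of the study, and the tool is meant to support counselling on fitness to drive. An accuracy of at least 80% could be reported as agreeing with the hypothesis even if hardly any unsafe driver was identified. A tool that finds most unsafe drivers, at the price of some false alarms, could fall short. A cut-off chosen to maximise overall accuracy would also be drawn towards missing unsafe drivers.

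**Working it through.** **The plan's own figure.** Section 10 gives N = 77 for a three-predictor regression with an average effect, alpha 0.05 and power 80%. Taking the average effect as f² = 0.15 (assumption: the conventional value), the overall F test with noncentrality f²·N and 3 and N − 4 degrees of freedom has power 0.796 at N = 76, 0.802 at N = 77 and 0.819 at N = 80. N = 77 reproduces, so the sample size is not in dispute.

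**Inputs.**
- Benchmark: 80% (section 3, hypothesis 3).
- Group sizes: 40 and 40 (section 7).
- Failure rate in the impaired group, pE: 13.6% (section 3, for patients with mild cognitive impairment; applying it to this group is an assumption).
- Failure rate in controls, pC: not given; assumed range 0% to 13.6%.

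**All-safe rule.** Expected unsafe drivers = 40·pE + 40·pC. Accuracy = 1 − (pE + pC)/2. Sensitivity is 0% throughout. In the impaired group alone, accuracy is 1 − 0.136 = 86.4%. The last column is the exact probability (sum of two binomials) that at most 16 of 80 drivers are unsafe, so that the rule's observed accuracy reaches 80%.

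| pE | pC | Expected unsafe of 80 | All-safe accuracy | Chance of observed accuracy ≥ 80% |
|---|---|---|---|---|
| 13.6% | 0% | 5.4 | 93.2% | about 100% |
| 13.6% | 5% | 7.4 | 90.7% | 99.9% |
| 13.6% | 10% | 9.4 | 88.2% | 98.9% |
| 13.6% | 13.6% | 10.9 | 86.4% | 96.1% |

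**Tools that do detect unsafe drivers.** Accuracy = sensitivity × prevalence + specificity × (1 − prevalence).
- At 80% sensitivity and 80% specificity, accuracy is 80% at any prevalence, below the all-safe rule in every row above.
- At 90% sensitivity and 78% specificity, accuracy is 0.90 × 0.068 + 0.78 × 0.932 = 78.8% with 6.8% unsafe, and 0.90 × 0.136 + 0.78 × 0.864 = 79.6% with 13.6% unsafe. This tool misses the benchmark.

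**Where the benchmark becomes informative.** The all-safe rule scores exactly 80% when pE + pC = 0.40, that is, with 16 of 80 unsafe. Examples are pE = 40% with pC = 0%, or pE = 30% with pC = 10%. Above that the position reverses: pE = 50% with pC = 0% gives the all-safe rule 75%.

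**Precision of sensitivity.** With 5 to 11 unsafe drivers, exact 95% confidence intervals are wide: 28% to 99% for 4 of 5 detected, and 48% to 98% for 9 of 11.

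**The case against.** **The base rate is borrowed.** The 13.6% refers to patients with mild cognitive impairment. The study's impaired group reaches down to MMSE 18, is also called mild to moderate, and includes affective, psychotic and neurotic disorders. Section 3 itself describes the risk in dementia as particularly high. Nor need unsafe on the WAFAB mean the same as failing the cited on-road test. With 40% unsafe in the impaired group and 5% in controls, for example, the all-safe rule would score 77.5%, below the bar. This stands, and it makes the point conditional. But the protocol offers no figure near that level.

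**Hypothesis 3 has a second part.** A reader might infer that a tool detecting nobody would pass the whole hypothesis. The text does not support that. The tool must also beat single tests. If each single test is cut for best accuracy on the same data, an extreme cut-off reproduces the all-safe rule, so an empty tool can only tie. How the single tests would be cut is not stated. The second part still does not repair the benchmark, because it is expressed in the same measure: a tool with useful sensitivity could lose to a single test that flags almost nobody.

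**The planning effect.** A reader might also infer that the effect size in section 10 contradicts the 80% target. It does not. The assumption that certain tests "can predict driving behavior with an average effect size" concerns TMT-L parts A and B and the LAT in a sample-size regression, not the screening tool. Section 10 reports average to large effects in the literature, and section 3 argues that test combinations predict better than single tests.

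**It is an expectation, and an SAP may add measures.** Section 10 attaches no formal test to the 80%, and sensitivity, specificity and AUC may be planned elsewhere. Their absence here is not the finding. The finding is that the one benchmark the protocol does fix is uninformative at its own base rate; extra measures would not make that threshold meaningful.

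**Conclusion.** The concern holds in conditional form. At the only failure rate the protocol gives, the 80% benchmark lies 6.4 to 13.2 percentage points below the accuracy of calling every driver safe (86.4% to 93.2%). This rests on 13.6% unsafe in the impaired group, 0% to 13.6% in controls, and equal groups of 40. It ceases to hold once more than 16 of 80 drivers are unsafe, which is possible in this population but not supported by any figure in the protocol. Under the stated assumptions about 5 to 11 unsafe drivers are expected, too few to confirm a sensitivity claim. The sample-size calculation is unaffected.

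**What to change.** In hypothesis 3 and section 10:

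1. Fix in advance which WAFAB result counts as unsafe. Sensitivity and specificity cannot be computed without this.
2. Judge the tool by sensitivity for unsafe drivers and specificity (or balanced accuracy), together with the AUC, all with 95% confidence intervals.
3. Make the comparison with single tests on the same measures.
4. If overall accuracy is kept, compare it with the observed no-information rate and not with 80% alone.
5. State that, with about 5 to 11 unsafe drivers expected under the assumption above, hypothesis 3 is estimation and not confirmation.

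The cost is one agreed definition, a reworded hypothesis and a few lines in section 10, with no new data. The downside is that the stated target becomes harder to reach and the sensitivity estimate will be visibly imprecise.

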**5. Outcomes**

**Primary outcomes**
Primary outcomes comprise performance in the neuropsychological assessment, especially in domains of attention, visuospatial abilities and executive functions.
Furthermore performance in the on-road assessment – at specified observational points - can be measured distinctively regarding errors made in categories like longitudinal control, lateral control and cognition. Every observational sequence is additionally rated on an 11-point rating scale.

**Secondary outcomes**
In addition sociodemographic, clinical and driving specific data will be analyzed with respect to their influence on the prediction of driving behavior.

**6. Study design**
The study is designed as a monocentric, non-randomized cross-sectional-study at the kbo-Inn-Salzach-Klinikum Wasserburg/Inn. Cut-off-scores in the MMSE of < 27 and ≥ 18 allocate the participants to the experimental group of subjects with mild cognitive impairment. Subjects with a MMSE-score ≥ 27 will be assigned to the healthy control group. We expect the recruitment period to last about 24 months. Each of these groups undergo the same assessment procedure. Blinding is only possible for the driving instructor.

**7. Study population**Women and men with an age ≥ 50 years, who possess a valid driver licence and who are active drivers, i.e. have been driving regularly the last three month before participation, and speak fluently German language can participate in the study. Regarding possible use of medication an exact documentation and clarification of potential adverse effects on on-road driving should be carried out in the context of anamnesis. Subjects who are under dose escalation or medication shifts will be excluded. The consent ability has to be checked, doubts about it also lead to exclusion. 40 subjects with mild to moderate cognitive impairment and 40 healthy control subjects will be assessed, parallelized regarding age, education, sex, driving experience and mileage per year.

*General exclusion criteria for all participants (based on annex 4, statutory order of driving licences)*

- Current severe dementia (MMSE < 18)
- Current severe psychiatric, neurological or internistic disease
- Visual impairment (visual acuity worse than 60%; visual field <140°, double-vision, hemi-neglect)
- No fluent German in speech and writing

*Specific criteria for the experimental groups*Healthy subjects (CG):

- ≥ 50 years
- German as first language respectively German-speaking since early childhood
- MMSE ≥27
- No record of severe psychiatric or neurological diseases
- Currently no internistic disease
- Currently no radio- or chemotherapy for cancer treatment

Cognitively impaired subjects (EG):

- ≥ 50 years
- First language German respectively German-speaking since early childhood
- MMSE ≥18 and <27
- Patients from the following ICD-10 diagnosis groups
  - Organic, including symptomatic disorders (F00-F09), N=20
  - Affective disorders (F30-F39), N=10
  - Schizophrenia, schizotypal or delusional disorders (F20-F29) / Neurotic, stress-related and somatoform disorders (F40-F48), N=10

For recruitment employees of the kbo-Inn-Salzach-Klinikum in Wasserburg/Inn will be addressed by mail and displays on the clinic campus as well as advertisement in relevant magazines and information-flyers. We request to make interested friends and other contacts aware of the study. Besides, patients will be informed about the study via the clinical departments for the diagnosis groups F00, F20 and F30 of the Inn-Salzach-Klinikum.

An estimation of the severity of possible psychiatric, neurological or internistic diseases will be made by the attending physician/psychologist of the particular department through anamnesis, information from the case history and medical reports. Assessing the healthy control group the principal investigator (psychologist) has to rely on the subjects’ truthful statements to make a classification.

**8. Study procedure**

Potential participants are initially informed about the study in written and verbally before given their written consent.

The assessments will take place at one term. Initially there is a briefing which contains the enlightenment (informed consent) and anamnesis as well as the allocation to experimental and control group by means of the MMSE-results. Subsequently the neuropsychological assessment is carried out which comprises the CFD test-battery (Cognitive Functions Dementia) and the Clock-Drawing-Test. The duration amounts to 120 minutes.

After a short recovery phase the on-road driving assessment is conducted. Finally a feed back is given on the results of neuropsychological assessment and the on-road driving. Moreover the participant is counselled regarding potential further therapeutic treatments.

| **Diagnostics**  Enlightenment  Consent  Anamnesis  Mini-Mental-State-Examination (MMSE)  Group allocation (by MMSE-Score)  Assessment of psychopathology   - Mini-SCL - PDQ   Assessment of driving competence (TQ-Drive)  Neuropsychological assessment   - CFD - Clock-Drawing-Test (CDT) - LAT (German adaption oft he JLO)   Duration: ca. 120 minutes | **On-road driving observation**  **& counselling**  On-road driving observation  Feedback oft he results   - Diagnostics - Driving behavior   Information leaflets  Duration: ca. 100 minutes |
| --- | --- |

Figure 1: Description of study procedure

*Enlightenment and anamnesis*a) Enlightenment and information brokerage
b) Informed consent
c) Anamnesis

*Deployed neuropsychological assessment tools*

| **Test** | **Mode** | **Duration** | **Annotation** |
| --- | --- | --- | --- |
| MMSE |  | 10 | CERAD-Plus Version |
| Mini-SCL, PDQ |  | 5 |  |
| Test-Set CFD | S1 | 60 | Standard mode plus shortened VISCO S3 mode |
| CDT |  | 3 |  |
| LAT | S1 | 10 |  |
| Total |  | 83 |  |

Table 1: Overview of the neuropsychological assessment

a) Mini-Mental-State-Examination (MMSE) – duration ca. 10 minutes
The Mini-Mental-State-Examination (Folstein et al., 1975)40 is a screening tool applicable in clinical practice to assess cognitive deficits. It is considered to be a reliable tool for initial examination of patients, e.g. in the context of dementia, as well as follow-up monitoring. The Mini-Mental-State-Examination is carried out as an interview with the patient. On the basis of 9 set of tasks central cognitive domains are checked (temporal and local orientation, memory retention, attention, language and speech comprehension, reading, writing, drawing and calculating). The MMSE tasks comprise both answering of questions and performing simple actions.

b) Assessment of subjectively perceived complaints and symptoms
The PDQ (Perceived Deficits Questionnaire; Fehnel et al., 2016)41 is utilized for the self-rating of cognitive deficits and allows for statements about the subjectively in everyday life perceived cognitive complaints of the patients and an estimation of its appearance and frequency. The reference period covers the last seven days.
The Mini-Symptom-Checklist (Mini-SCL; Franke, 2017)42 measures the subjectively perceived complaints using predefined physical and psychic symptoms over the last seven days.

c) Assessment of driving competence (TQ-Drive) – duration ca. 7 minutes
This computer based questionnaire assesses driving anamnestic information such as driving experience in terms of mileage per year, personal importance of the motor vehicle, driving difficulties and avoidance behavior etc. It provides a general impression of the individual driving performance and potential traffic-relevant risk factors.

d) Test-Set Cognitive Functions Dementia (CFD) – duration ca. 60 minutes
The test-set CFD measures neuropsychological domains relevant for neurocognitive disorders (according to DSM-5). By means of the CFD test-set cognitive performances in neuropsychological domains like attention, verbal long-term memory, executive functions, expressive speech and perceptual motor functions can be assessed. Table 2 lists all individual tests used in the study in order of display including duration of implementation.

|  | Dimension | Test | Subtest | Duration |
| --- | --- | --- | --- | --- |
| 1 | Semantic fluency | WIWO | S1 | 3 |
| 2 | Lexical fluency | WIWO | S3 | 4 |
| 3 | Learning ability | AWLT  (Subtest 1) | S1 | 7 |
| 4 | Alertness (intrinsic-visual) | WAFA | S2 | 2 |
| 5 | Brief delayed recall | AWLT  (Subtest 2) | S1 | 2 |
| 6 | Divided attention | WAFG | S3 | 9 |
| 7 | Processing speed | TMT | S1 | 1 |
| 8 | Cognitive flexibility | TMT | S1 | 1 |
| 9 | Working memory, spatial | CORSI | S7 | 8 |
| 10 | Long delayed recall and discrimination | AWLT  (Subtests  3 und 4) | S1 | 4 |
| 11 | Object naming | WOBT | S1 | 5 |
| 12 | Visuo-construction | VISCO | S3 | 7 |

Table 2: Dimensions and tests of the CFD test-set

The tests quoted in table 2 are presented in detail below.

On 1. and 2.: Vienna Verbal Fluency Test (WIWO)
Verbal Fluency describes a person’s ability to generate and reproduce words according to defined rules. There are two subdimensions of verbal fluency: semantic and lexical verbal fluency. Semantic verbal fluency describes a person’s ability to reproduce words of a specific category (e.g. first names) whereas lexical verbal fluency determines the ability to generate words beginning with specific letters.
Both subdimensions of verbal fluency are assessed in the CFD test set using the WIWO test. The respondent’s task is to name as many words as possible within two minutes that belong to a certain category (semantic verbal fluency: test form S1) or that start with a certain letter (lexical verbal fluency: test form S2). When the CFD test set is scored the main variable “verbal fluency” is calculated based on the number of correctly named words.

On 3., 5. and 10.: Auditory Word List Learning Test (AWLT):
Long-term memory describes the ability to retain information long-term, integrate it into one’s knowledge base and retrieve it when needed. Long-term memory contains all information that can be remembered for longer than a period of a few minutes. The process of learning is divided into the stages of encoding consolidation and recall.
Verbal long-term memory is assessed in the CFD test set with the AWLT test using test form S1. A list of 12 words is used as learning material in AWLT. The test implements a learning assessment method of four learning runs and short (5-minute break) and long (20-minute break) delayed free recall. As many words as possible must be freely reproduced immediately after each learning run and after the brief and long delays. The word list is not displayed again during the two recall phases. At the end, a list of 24 words is presented to the respondent: 12 words from the learning phase list and 12 new words intended as distractors. The respondent’s task is to say which of the 24 words were on the word list and which were not. The scoring of the CFD test set defines “learning total”, “short-term delayed recall”, “long-term delayed recall” and “recognition” as the main measurement variables.

On 4.: Perception and Attention Functions – Alertness (WAFA)
Alertness pertains to the core dimensions “Attention”. The construct of alertness encompasses both the state of ongoing general wakefulness and readiness to react (tonic alertness) and the ability to increase the level of attention quickly in response to a cue (phasic alertness). If stimuli are presented without a cue, the term “intrinsic alertness” is also used. Unlike phasic alertness, intrinsic alertness involves a self-generated increase in the level of alertness.
Alertness is measured in the CFD test set with the WAFA test using test form 2. The WAFA test measures reaction time in response to simple visual stimulus material (black circle on white background). The main variable that is reported when scoring the CFD test set is “Mean Reaction Time”.

On 6.: Perception and Attention Functions – Divided Attention (WAFG)
Divided attention pertains to the core dimension “Attention”. Divided attention is the ability to direct one’s attention toward several information channels simultaneously. For example, division of attention is required in “dual tasks” in which two information channels must be monitored simultaneously. If a relevant event occurs in one or both channels, the respondent must react as quickly as possible.
Divided attention is measured in the CFD test set with the WAFG test using test form 3. The respondent receives stimuli on one visual and one auditory channel. The task is to constantly monitor both channels to determine whether one of the target stimuli (square or high tone) changes twice in succession. The main variable that is reported when scoring the CFD test set is “Mean Reaction Time”.

On 7.: Trail-Making Test – Langensteinbach Version (TMT) Part A:
Processing speed is the basal ability to process simple stimuli quickly and with confidence without it being essential to involve higher cognitive, sensory or motor processes. The CFD test set assesses a fundamental measurement of processing speed using part A of the TMT test using test form S1. The task involves multiple circles containing the numbers from 1 to 25 that are presented simultaneously on the screen. These must be linked in ascending order as quickly as possible. The main variable that is reported when scoring the CFD test set is “Working Time Part A”.

On 8.: Trail-Making Test – Langensteinbach Version (TMT) Part B
Part B of the TMT assesses cognitive flexibility using test form S1. Cognitive flexibility is the ability to shift at will between different reference systems when this is required. The respondent’s task is to link circles containing the numbers 1 to 13 and the letters A to L alternately in ascending order. The main variable reported when the CFD test set is scored is the “Working Time in Part B”.

On 9.: CORSI Block-Tapping Test (CORSI)
Spatial working memory pertains to the core dimension “Executive Functions”. Working memory comprises the ability to process memory content in the mind in order to carry out tasks and achieve goals. Working memory can therefore be regarded as the ability to retain and process information that has been briefly presented and that is relevant to solving a task that is currently at hand.
(Spatial) working memory is assessed in the CFD test set with the CORSI test using test form S7. In this test nine blocks are shown on the screen. Each item involves a hand icon that moves about the screen, tapping on a certain number of blocks in a particular order. The respondent must tap the blocks in reverse order (backwards). The length of the sequences increases over the course of the test. It begins with a sequence of two taps and ends at the latest of a sequence of nine taps. The test terminates as soon as three successive sequences have been incorrectly tapped. The main variable reported when the CFD test set is scored is the variable “Immediate Block Span Backward”.

On 11.: Vienna Object Naming Test (WOBT)
Object naming pertains to the core dimension “Expressive Language”. Object naming describes the ability to recognize objects and to recall and reproduce the relevant names from one’s vocabulary. Declarative memory thus plays a role in test performance. Object naming is measured in the CFD test set with the WOBT test using test form S1. In the test, pictures depicting different objects are shown to the respondent and it is the respondent’s task to name these objects correctly. Should the respondent not be able to name the object, a lexical cue (the first letter of the target name) and after that a semantic cue (description of the target object without naming the target word) is given if needed. If none of these cues help the respondent to name the object, move on to the next item. The maim variable reported when the CFD test set is scored is the number of immediate correct namings (“Correct Naming Immediate”).

On 12.: Visuoconstruction Test (VISCO)
Visuoconstruction ability pertains to the core dimension “Perceptual Motor Functions”. Visuoconstruction refers to the ability of recognizing individual elements of shapes or objects and (re)constructing these shapes or objects by assembling the individual elements.
This ability is measured in the CFD test set with the VISCO test using test form S3. The test involves 16 tasks. For each task a shape made up of several equilateral triangles is shown as a target shape. Only the overall outline of the figure is visible, not the outline of the individual triangles themselves. The respondent’s task is to visualize the composition if the target figure and assemble it in an input field with the triangles that point both upwards and downwards. The respondents are given 60 seconds to solve each item. As soon as a person fails to complete the correct figure three times in succession, the test is automatically terminated. The main variable reported when the CFD test set is scored is the variable “Visuoconstruction Ability”.

e) Clock Drawing Test (CDT)
The Clock Drawing Test (Shulman, 1993)43 is a commonly used screening tool to assess visuoconstructive abilities for example during first diagnostic confirmation of dementia. The patient is asked to draw a clock face and enter the position of the clockhands for a certain time. The implementation takes about three minutes. It is possible to draw inferences about the extent of the dysfunction based on the deviations of depiction from “normal-performance” (segmentation of the clock face, type face of the digits, absence of the clockhands). In doing so 1 to 6 points are assigned depending on the deviation, whereas a score ≥ 3 can be classified as an indication of dysfunctions in this domain.

f) Line Adjustment Test (LAT)
Cerebral visuospatial processing are commonly differentiated into four categories: spatial-perceptual, spatial-cognitive, spatial-constructive and spatial-topografical performances. Spatial-perceptual performances are comparatively elementary. These include identification of the position of the subjective main space axes (vertical, horizontal), orientation (inclination), registration of the space within objects (length, size) and between objects (distances), recognition of positions and shapes, estimation of forms and also more specific performances like line halving and subjective straight orientation.
The LAT assesses basal spatial-perceptive abilities, especially the ability to estimate the inclination of lines and angles between lines. On one side of the screen two arrows are shown touching each other on the base in a certain angle. On the other side of the screen there is a clock-face. On that clock-face those two numbers have to be marked which are being pointed at by the arrows if those were situated in the middle of the clock-face. The main variable is the number of correctly handled tasks.

g) On-road driving assessment
The Wasserburg on-road driving assessment (WAFAB) is conducted by a certified driving instructor who is experienced assessing drivers with neurological or psychiatric disorders and a psychological technical assistant in a standardized driver instruction vehicle. It comprises a 50 minute drive on a predetermined route of approximately 50 kilometers length with determined observational spots and has been tested and established in clinical practice over the last ten years. The driving instructor is blinded against group allocation. As a global measure every observation sequence will be rated on an 11-point Fitness-to-Drive-Scale44. The scale consists of three verbal categories (normal, limited, citical) and within each of them three numeric subcategories (high, middle, low). In addition the driving errors will be rated by trained persons regarding total amount of errors, tactical errors with respect to longitudinal control (speed too high, time headway too low/tailgating), operational errors with respect to lateral control (lane departures/bad lane keeping, lateral distance to objects/vehicles too low) and cognitively based tactical errors (errors in changing/choosing lane, driving on impermissible lanes, securing behavior, communication, navigation errors) on determined observational spots; as an ancillary category critical situations (threats to other traffic participants, collisions) will be gathered.

**9. Benefit-risk analysis**At the time of assessment the participants are subjected to a test situation. This could be burdensome and provoke unpleasant feelings. However there is a detailed enlightenment about possible load factors. At each instant direct contact to psychologically trained staff is assured to guarantee quick announcement of complaints and an immediate reaction. Moreover, the study procedure can be cancelled at any time by the participants. The occurrence probability of further risks is estimated low. At any given moments participants can call for rest periods. In context of their participation, participants receive a free and professional assessment of their driving safety and are reimbursed with 25 Euro.
Establishing a new fitness-to-drive screening it is essential to know its predictive validity and accuracy. We consider the benefit-risk ratio to be fortunate because of the minor risks and major benefits of an economical and highly predictive fitness-to-drive screening for clinical daily routine.

